## Abstract

**Background:**

To ensure patients continue to get early access to antibiotics at admission, while also safely reducing antibiotic use in hospitals, one needs to target the continued need for antibiotics as more diagnostic information becomes available. UK Department of Health guidance promotes an initiative called ‘Start Smart then Focus’: early effective antibiotics followed by active ‘review and revision’ 24–72 h later. However in 2017, < 10% of antibiotic prescriptions were discontinued at review, despite studies suggesting that 20–30% of prescriptions could be stopped safely.

**Methods/design:**

Antibiotic Review Kit for Hospitals (ARK-Hospital) is a complex ‘review and revise’ behavioural intervention targeting healthcare professionals involved in antibiotic prescribing or administration in inpatients admitted to acute/general medicine (the largest consumers of non-prophylactic antibiotics in hospitals). The primary study objective is to evaluate whether ARK-Hospital can safely reduce the total antibiotic burden in acute/general medical inpatients by at least 15%. The primary hypotheses are therefore that the introduction of the behavioural intervention will be non-inferior in terms of 30-day mortality post-admission (relative margin 5%) for an acute/general medical inpatient, and superior in terms of defined daily doses of antibiotics per acute/general medical admission (co-primary outcomes). The unit of observation is a hospital organisation, a single hospital or group of hospitals organised with one executive board and governance framework (National Health Service trusts in England; health boards in Northern Ireland, Wales and Scotland). The study comprises a feasibility study in one organisation (phase I), an internal pilot trial in three organisations (phase II) and a cluster (organisation)-randomised stepped-wedge trial (phase III) targeting a minimum of 36 organisations in total. Randomisation will occur over 18 months from November 2017 with a further 12 months follow-up to assess sustainability. The behavioural intervention will be delivered to healthcare professionals involved in antibiotic prescribing or administration in adult inpatients admitted to acute/general medicine. Outcomes will be assessed in adult inpatients admitted to acute/general medicine, collected through routine electronic health records in all patients.

**Discussion:**

ARK-Hospital aims to provide a feasible, sustainable and generalisable mechanism for increasing antibiotic stopping in patients who no longer need to receive them at ‘review and revise’.

**Trial registration:**

ISRCTN Current Controlled Trials, ISRCTN12674243. Registered on 10 April 2017.

**Electronic supplementary material:**

The online version of this article (10.1186/s13063-019-3497-y) contains supplementary material, which is available to authorized users.

## Background

Antimicrobial resistance is one of the most important global public health risks recognised by the UK government [1] and the World Health Organization (WHO) [2], with increasing impacts on health [3]. It is increasing year-on-year, particularly in common Gram-negative bacteria [4, 5]; for example, the incidence of *Escherichia coli* bloodstream infections resistant to the most commonly used antibiotics has quadrupled over the last decade in Oxfordshire [6].

The only way to reduce the selective pressure on bacteria to develop resistance is to reduce antibiotic use [7, 8]. Resistant strains emerge rapidly in faecal [9] and nasal flora [10–12] during antibiotic treatment. Detectable resistance in these carried organisms wanes over time, but it can persist [13] and is still associated with developing antibiotic-resistant infections [14, 15], as is prior antibiotic use [15, 16]. Reducing population-level antibiotic consumption can significantly reduce drug resistance [17], although this is not a simple cause-effect relationship. Most bacterial resistance is due to genes carried on mobile genetic elements which move within and between bacterial species. Thus, removing selection pressure from one antibiotic will not always lead to loss of resistance, e.g. if other beneficial genes (or genes conferring resistance to other antibiotics still in use) are co-carried on the same mobile element [18–20]. Nevertheless, countries with higher antibiotic consumption generally have higher rates of antibiotic-resistant infections [21].

Whilst hospital prescribing accounts for < 20% of the antibiotics consumed in England, around two-thirds of prescriptions for ‘broad-spectrum’ agents (active against a wide variety of bacteria, including some antibiotic-resistant strains) are made in hospitals [5]. These broad-spectrum antibiotics have the greatest potential to drive future resistance, and, in contrast to primary care, hospital prescribing continues to increase (by 7% over 2013–2018 [5]). Aside from resistance, antibiotics are also associated with non-trivial rates (~ 20%) of adverse drug reactions [22].

Avoiding or delaying prescription are two strategies that successfully lower antibiotic consumption in primary care [23, 24]. However, in contrast to primary care patients, a considerable proportion of those presenting to hospital will genuinely have bacterial infections and need antibiotics. If a patient has a life-threatening bacterial infection, delays in administering effective antibiotics of even one hour increase mortality risk [25]. The challenge is accurately identifying these patients and their infecting microorganisms, which is difficult and takes time. This provides the rationale for prescribing broad-spectrum antibiotics whenever infection is suspected at admission (see e.g. ‘Surviving Sepsis’ [26]), since these should kill any infecting bacteria whilst (in theory) not harming patients without bacterial infections.

To ensure patients continue to get early access to antibiotics at admission, the safe reduction of antibiotic use in hospitals therefore needs to target the continued need for, and choice of, antibiotics as more diagnostic information becomes available. 2011 Department of Health (DH) guidance promotes an initiative called ‘Start Smart then Focus’ [27, 28]: early effective antibiotics followed by active ‘review and revision’ 24–72 h later. Five options are recommended: stop; switch from intravenous to oral administration; continue and review again; change (if possible to antibiotics with narrower spectrum of activity); or move to outpatient intravenous antibiotic therapy.

However, a 2013 survey of National Health Service (NHS) antibiotic pharmacists found that although 95% of 105 responding English trusts included early antibiotic review in their policies/guidelines, only 48% conducted any compliance monitoring [29]. Where compliance was monitored, relatively few (< 20%) prescription changes of any kind were made. This agrees with studies reporting clinicians’ reluctance to modify antibiotic prescribing decisions made by others, even when a patient’s clinical status has evolved [30] and reflects the complexity of decision making on antibiotic prescribing [31]. Trust policies frequently recommended antibiotic durations of ≥ 7 days [29], suggesting lack of review could lead to substantial overuse. Even by 2017, < 10% of antibiotic prescriptions were discontinued at review [32], despite studies suggesting that 20–30% of prescriptions could be stopped safely [33]. Despite considerable variation in local guideline-recommended antibiotic duration and practice [29], there are no data showing whether or not trusts which routinely use fewer antibiotics have higher rates of adverse outcomes.

This failure of prescribers to change or stop antibiotics is perhaps unsurprising given the lack of evidence to inform how ‘review and revise’ should be implemented. Of 221 hospital antimicrobial stewardship interventions included in a Cochrane review [34], only 14 even collected duration of antibiotic therapy as an analysable outcome, let alone directly targeted it; many of these studies evaluated the introduction of procalcitonin testing as a mechanism to reduce antibiotic durations. Other interventions included introducing guidelines/policies and education/feedback. Interventions specifically designed to reduce antibiotic duration were not evaluated as a category, but overall duration of antibiotic treatment decreased by 1.95 days with stewardship interventions. One large study (*n* = 462) [35] found an intervention incorporating face-to-face pharmacist feedback significantly reduced antibiotic durations for lower respiratory tract infections in intensive care. However, another study found no impact of prescription review by telephone [36], illustrating the importance of specific intervention components.

The challenge is developing feasible, sustainable and generalisable ‘review and revise’ interventions given the complexity of hospital antibiotic prescribing. Doctors need to balance the risks of under-treating infection in patients against risks of antibiotic-resistant infections in the future, making practical choices about specific drug, dose and duration given clinical indication, within the cultural context of multidisciplinary secondary care [31]. In the near future, faster and more accurate diagnostic tests for infection will likely become available, reducing the time to identify an infecting organism and its antibiotic susceptibilities. It is highly unlikely that these tests will remove the need to prescribe broad-spectrum antibiotics for severely ill patients at admission, but they will bring the time frame for ‘review and revise’ decisions forwards and increase potential gains from optimally implementing this ‘review and revise’ approach.

## Methods

### Objective

The primary objective of ARK-Hospital is to evaluate whether a multifaceted ‘review and revise’ behavioural intervention targeting healthcare professionals involved in antibiotic prescribing or administration in inpatients admitted to acute/general medicine (the largest consumers of non-prophylactic antibiotics in hospitals [37]) can safely reduce total antibiotic burden in acute/general medical inpatients by at least 15%. The primary hypotheses are therefore that the introduction of the behavioural intervention will be non-inferior in terms of 30-day mortality post-admission for an acute/general medical inpatient and superior in terms of defined daily doses (DDDs) of antibiotics per acute/general medical admission.

### Design

The study comprises three phases: a feasibility study (phase I), an internal pilot trial (phase II) and a cluster (organisation)-randomised stepped-wedge trial (phase III) in which each organisation acts as its own control.

In the phase I feasibility study, the intervention was implemented in one organisation on 18 April 2017 to test the feasibility and acceptability of trial procedures (e.g. clinical research governance, trial documents), the trial intervention (e.g. usage, engagement, adherence, completion, fidelity) and data collection procedures (e.g. audit results, questionnaires, electronic health record data). (Cross ELA, et al.: Adaptation and Implementation of the ARK (Antibiotic Review Kit) Intervention to Safely and Substantially Reduce Antibiotic Use in Hospitals: a Feasibility Study, submitted. [38])

The phase II internal pilot formed the first phase of the substantive trial evaluating the impact of the intervention package on healthcare professionals and inpatients/carers. The intervention was iteratively implemented in three organisations between 25 September 2017 and 20 November 2017, using the ACCEPT approach [39] to identify necessary refinements and as the basis for the decision to include long-term follow-up from these phase II pilot sites within the main trial evaluation (phase III).

In the phase III main trial, the intervention is being implemented in two to four organisations per month over 18 months from 12 February 2018 to 24 June 2019, to reach the total sample size of a minimum of 36 organisations for evaluation (including phase II internal pilot sites). A further 12 months’ follow-up in all organisations will assess the sustainability of any intervention effect.

The unit of randomisation is the organisation, a single or group of hospital(s) organised with one executive board and governance framework. In England these are called *trusts*; in Northern Ireland, Scotland and Wales they are called *health boards*. Organisation is the unit of randomisation because the intervention targets healthcare professionals who frequently move between teams within an organisation. Patient- or ward/team-level randomisation is therefore infeasible because of a high certainty of contamination. A stepped-wedge design is more efficient for the same number of units than a parallel group cluster-randomised trial when the intra-class correlation coefficient is relatively large and the cluster sizes are large, because each unit acts as its own control, reducing variability [40]. Organisations are very large units of randomisation, but as explained previously, this is necessary because clinical teams are shared across organisations so there is no smaller unit of randomisation that will avoid contamination. Because antibiotic prescribing activities are based on local organisation guidelines and culture, we also expect within-organisation variation to be much smaller than between-organisation variation. Thus, we anticipate that the stepped-wedge design will be more efficient for this specific evaluation study. The stepped-wedge design also ensures that all participating organisations have the opportunity to receive the intervention at some point. This is important given the strong interest from organisations in interventions which could reduce antibiotic consumption, in the face of the emphasis on reducing inappropriate antibiotic use in hospitals from DH and wider government and financial incentives supporting such reductions [41, 42].

Figure 1 shows how the patient population is defined from health records. Figure 2 illustrates the analysis model. Figure 3 shows the ARK schedule of enrolment, interventions and assessments and Fig. 4 the flow diagram. The Standard Protocol Items: Recommendations for Interventional Trials (SPIRIT) checklist is provided as Additional file 1.

**Fig. 1 Fig1:**
[figure not shown]
Defining the patient population from routinely collected electronic health records

**Fig. 2 Fig2:**
[figure not shown]
Analysis model

**Fig. 3 Fig3:**
[figure not shown]
ARK schedule of enrolment, interventions, and assessments (SPIRIT figure). * Healthcare organisations are recruited to the study before enrolment but at varying calendar times, based on the fact that they can provide historical patient electronic healthcare record data pre-implementation. They are allocated an implementation date based on the stepped-wedge design. ** Follow-up finishes 12 months after the last randomised organisation implements the intervention, estimated June 2020. † There are no formal assessments. Outcomes are assessed using routinely collected electronic health records from patients admitted to acute/general medicine over the entire study period, pooled periodically during the trial

**Fig. 4 Fig4:**
[figure not shown]
SPIRIT 2013 Checklist: Recommended items to address in a clinical trial protocol and related documents

### Inclusion/exclusion criteria

Organisations from England and the three devolved nations (Northern Ireland, Wales and Scotland) are eligible if they are (1) organisations admitting patients to (adult) acute/general medicine (the target patient population) (acute or district general trust in England); (2) willing to implement the intervention in healthcare professionals involved in antibiotic prescribing or administration in adult acute/general medicine and able to identify a local ‘champion’ to lead this; and (3) able to provide the required routine electronic data on adult patients admitted to acute/general medicine over the required time periods (see the discussion in subsequent sections). There are no exclusion criteria. Organisations are identified and approached through professional networks, the Society for Acute Medicine, through the clinical research networks and through word of mouth. Study sites are listed on http://www.arkstudy.ox.ac.uk/about/.

### Intervention

This protocol will test a complex behavioural intervention for healthcare professionals designed using a ‘person-based approach’ [43], based on stakeholder workshops and qualitative studies with healthcare professionals and patients, to increase the acceptability, feasibility and effectiveness of the ‘review and revise’ component of the DH ‘Start Smart then Focus’ strategy. The intervention includes several components (Santillo M, et al.: Intervention Planning for the ARK (Antibiotic Review Kit) Intervention: a Digital and Behavioural Intervention to Safely Review and Reduce Antibiotic Prescriptions in Acute and General Medicine, submitted [44]). They are:An evidence-based educational and motivational website (with mobile-friendly version) including training in the ARK decision aid (‘online training’)The ARK decision aid to classify initial antibiotic prescriptions based on risk of infectionData collection on rates of review and revise, use of the decision aid and rates of stopping, alongside regular and supportive discussions with clinical teams (e.g. through peer-led seminars or ward rounds) to support staff with implementation and address any barriers or concernsA patient leaflet which healthcare professionals can provide to acute/general medical inpatients and their carers to inform and reassure patients that their antibiotics may be stopped, without requiring increased consultation time, and to instruct them to ensure healthcare professionals are aware if their symptoms worsen. (Mowbray F, et al.: Patient Engagement with Antibiotic Messaging in Secondary Care: a Qualitative Study of the ‘Review & Revise’ Experience, submitted [45]).

The intervention includes an implementation toolkit to help the local champion and the implementation team adopt and adapt the intervention to their local structures. Relevant local factors include how acute/general medical services are provided (e.g. acute medical unit, clinical decision unit, emergency department); when/if staff change post the initial admission ‘take’ round; who is involved in decisions about continuing or not continuing antibiotics (emergency department, specialists, acute/general physicians); and local prescribing systems (e.g. paper vs electronic).

To avoid contamination, complete information about the intervention is released to the local champion at the point of randomisation, which is 3 months before anticipated organisation-wide implementation. The intervention is not blinded; patients who receive the leaflet or who are aware of study posters will also not be blinded.

### Randomisation

The phase III main trial uses an organisation-randomised stepped-wedge design in which interventions are successively implemented across different organisations over time.

The stepped-wedge cluster-randomised main trial uses calendar-time blocked randomisation. The randomisation list was drawn up in blocks of 6 before the trial started. Organisations were added to a separate list of trial sites based on the date when they joined the ARK network, divided into groups of 6, with the implementation date for each organisation then randomly assigned by the randomisation list (i.e randomisation stratified by these blocks). This is feasible, because all research data on which the intervention is evaluated are routine electronic health record data that are completely independent of the trial. Thus, they are available historically and collected in the same way, regardless of the date of randomisation/implementation— there are no research-specific outcome data in the trial (details in a subsequent section). Organisations have no control over which block they are allocated to or to their randomisation date: 24 organisations had already joined the network at the start of randomisation. This was a pragmatic decision based on the fact that trusts in the main trial would be randomised over 18 months, and in the current NHS climate it is impossible to get NHS trusts to agree to join a programme to reduce antibiotic use where they might not get the intervention for 18 months. All comparisons will be made before and after implementation in the same trust (see the following paragraphs), since any comparison across trusts pooling time will be irretrievably confounded by various organisational changes internally and externally.

In practice, the local champions need some lead time to get an implementation team together, to identify the essential individuals who drive prescribing decisions for acute/general medical inpatients at the organisation (in whom training uptake will be assessed) and to arrange meetings with staff before implementation. Randomisation therefore occurs 3 months before the target ‘implementation date’ (baseline), and the implementation toolkit contains a focused set of activities from this randomisation date through to implementation.

Randomisation uses computer-generated random numbers and is based on two to four organisations implementing per month (on Mondays), avoiding implementation dates over the summer holidays, Christmas and Easter. The allocation sequence has been generated by the Trial Statistician ([name]) and is concealed from everyone except the Trial Statistician. The Trial Statistician informs the Trial Manager of the next randomisation 5 days before the randomisation by email; the Trial Manager then informs the site by email on the randomisation day. Any organisation which withdraws from the trial between randomisation and randomised implementation date will be replaced, and their electronic research data will not be collected. They will be reported as a withdrawal.

### Follow-up

The intervention is delivered to healthcare professionals involved in prescribing or administering antibiotics, but outcomes are assessed in inpatients admitted to acute/general medicine (see the following section). Therefore, follow-up periods relate to calendar time before and after implementation intervention. Routinely collected electronic patient health data are therefore requested from each organisation from 1 February 2016 (2 years before the start of phase III), or as close to this as possible (or up to 2 years pre-implementation for feasibility and pilot organisations). Final data will be requested on 31 October 2020, 15 months after the last randomised implementation date, to allow 90-day mortality to be ascertained on the last patients admitted up to 12 months’ post the last randomised implementation date.

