The primary analysis method for binary outcomes will be logistic regression. This is done because, for mortality, data will be considered to be completely ascertained on the basis of routine checks that each organisation conducts against the national death registry, for example, to ensure that follow-up letters are not sent to patients who have died. Therefore, patients not recorded as dying in the national system will be assumed to be alive 30 days (co-primary outcome) and 90 days (secondary outcome) after admission. The death registry is not up to date in real time, and routine checks are only carried out periodically; the final data extract will be requested 6 months after the last included admission to ensure that ascertainment is as robust as possible. In-hospital mortality is completely ascertained by discharge codes. Further, for all binary outcomes, event rates are relatively low (5–10%), so there is little difference between analysing a cause-specific hazard or a competing risks subhazard. Analysing the outcome using logistic regression also facilitates visualisation of the estimated pre- and post-implementation trends, and the step change at implementation, against the observed percentages for each outcome per organisation. Sensitivity analyses will consider these as time-to-event outcomes and will consider competing risks from inpatient and out-of-hospital deaths as relevant for each specific outcome [53–55]. Negative binomial regression will be used to model antibiotic DDDs, incorporating over-dispersion and using different offsets as defined previously. Other antibiotic outcomes are planned to be analysed using ordinal logistic regression; however, if, for example, data are approximately normally distributed, either before or after transformation, linear regression may be used instead. Box-Cox-transformed length of stay will be analysed using normal linear regression. A sensitivity analysis will include stay only up to the point a patient was declared medically fit for discharge. A second sensitivity analysis will use quantile regression of the 90th percentile to assess effects at the extremes of the distribution.

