### Main trial status

The first organisation was randomised in the main trial on 13 November 2017 (under protocol version 4.0) to implement on 12 February 2018. The last organisation is planned to be randomised on 1 April 2019 to implement on 24 June 2019.

The current protocol is version 5.0 (5 November 2018). All protocols have been approved by the South Central Oxford C Research Ethics Committee (REC) (17/SC/0034) and the Confidentiality Advisory Group (CAG) (17/CAG/0015). Protocol 1.0 (16 December 2016) was submitted for REC and CAG approval for the three phases of the study. Version 2.0 (24 March 2017; phase I feasibility study) incorporated clarifications requested by REC and CAG including those on opt-out and the electronic health records analysis population, and increased preparation time from randomisation to implementation from 3 to 4 months based on experience preparing for the feasibility study. Version 3.0 (25 September 2017; phase II pilot study) included further clarifications on the analysis population based on advice from the Nuffield Trust and extension of process evaluation to include interviews. Version 4.0 (6 November 2017; phase III main trial) returned preparation time from 4 to 3 months based on experience in the internal pilot and removed an acceptability rating which had not been collected. Version 5.0 (5 November 2018) increased the number of organisations included in process evaluation and clarified how individuals would be recruited for these qualitative studies, adding eight criteria defining implementation fidelity and several other clarifications regarding objectives, outcome measures, withdrawal, population and analysis to align with the statistical analysis plan version 1.0.

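### The Follow-up and Statistical analysis sections give incompatible timings for the final data extract, and the earlier one shortens death ascertainment only for post-implementation admissions

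*Protocol article*

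**What the plan says.** All references are to the Methods of the protocol article.

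- **Follow-up.** "Final data will be requested on 31 October 2020, 15 months after the last randomised implementation date". The stated purpose is "to allow 90-day mortality to be ascertained on the last patients admitted up to 12 months" after that last implementation.
- **Statistical analysis.** "the final data extract will be requested 6 months after the last included admission to ensure that ascertainment is as robust as possible". The reason given is "The death registry is not up to date in real time, and routine checks are only carried out periodically". The same paragraph says "patients not recorded as dying in the national system will be assumed to be alive 30 days" (the co-primary) and likewise at 90 days (secondary). It adds that discharge codes capture in-hospital deaths completely.
- **Main trial status.** "The last organisation is planned to be randomised on 1 April 2019 to implement on 24 June 2019".
- **Fig. 3 caption.** "Follow-up finishes 12 months after the last randomised organisation implements the intervention, estimated June 2020".
- **Sample size.** Non-inferiority requires the whole 95% confidence interval for the relative change in mortality to lie within 0.95 to 1.05.

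**The concern.** The protocol describes one event, the final data request, by two rules that cannot both be met, and one of those rules disagrees with its own calendar date. An organisation's informatics department would not know which to follow.

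The choice affects the mortality data. The six-month wait is the plan's own protection against late death records, and anyone without a recorded death is analysed as a survivor. By spring 2020 every organisation has implemented, so deaths missed through an early extract can come only from post-implementation admissions. Effects are estimated before versus after within each organisation, so no concurrent control loses deaths at the same rate. Missing deaths at the end of the series would pull the post-implementation mortality trend down, and that trend is part of the primary comparison for the safety co-primary.

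**Working it through.** **Inputs.** Last implementation 24 June 2019 (Main trial status). Inclusion runs to 12 months after it (Follow-up, Fig. 3 caption), so the last included admission is about 24 June 2020. Stated request date 31 October 2020 (Follow-up). Alternative rule: last admission plus 6 months (Statistical analysis).

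**1. The stated 15 months does not reproduce.** 24 June 2019 to 31 October 2020 is 495 days; 495 / 30.44 = 16.3 months. Fifteen months after 24 June 2019 is 24 September 2020, 37 days earlier.

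**2. The six-month rule gives a third date.** 24 June 2020 + 6 months = 24 December 2020, which is 12 + 6 = 18 months after the last implementation and 54 days after 31 October. The conflict does not depend on the calendar: 15 months after implementation is 3 months after the last admission, not 6.

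**3. Time for a death to reach the records, for the last admission (24 June 2020).**

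| Request date | Days since admission | Left after day 30 (co-primary) | Left after day 90 (secondary) |
|---|---|---|---|
| 24 Sep 2020 (literal 15 months) | 92 | 62 | 2 |
| 31 Oct 2020 | 129 | 99 | 39 |
| 24 Dec 2020 (6-month rule) | 183 | 153 | 93 |

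**4. Admissions short of the plan's own standard.** At 31 October 2020, admissions up to 30 April 2020 have had six months. Those after it, to 24 June, cover 55 days, about 8 weeks. As a share of post-implementation time, assuming even admission rates, this is 55/863 = 6% in the first main-trial organisation (12 February 2018), 55/613 = 9% in one implementing around 20 October 2018, and 55/366 = 15% in the last.

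**5. Possible size.** The documents give no reporting lag, so the share of deaths missed is assumed at 2%, 5% or 10%. Weekly log mortality was set flat from 1 February 2016 to 24 June 2020, with a deficit of log(1 - share) in the last 8 weeks. The model intercept + trend + step + change in trend was fitted for each of 33 implementation dates (36 organisations less 3 pilots), evenly spaced from 12 February 2018 to 24 June 2019. Estimates were averaged. The effect at 12 months is step + 1 year x change in trend.

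| Share missed | Shift in 12-month effect |
|---|---|
| 2% | -0.4% |
| 5% | -1.0% |
| 10% | -2.0% |

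The components move in opposite directions. Across the 2% to 10% range the step change shifts by +0.3% to +1.7%. The change in trend therefore shifts by about -0.4 - 0.3 = -0.7% to -2.0 - 1.7 = -3.7% per year. A plain post-versus-pre contrast shifts by -0.2% to -1.0%.

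**6. What the 10% case requires.** Only out-of-hospital deaths can be missed. If these are 20% to 40% of 30-day deaths (an assumption; no figure is given), missing 10% of all deaths means missing 0.10/0.40 = 25% to 0.10/0.20 = 50% of them.

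**The case against.** The strongest reply is that this is a slip in wording with little consequence. Several parts of it stand.

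- The co-primary is 30-day mortality. At 31 October it has 99 days for late reporting, even for the last patient. A reader might take the 39-day figure as the safety margin for the co-primary, but it belongs to 90-day mortality, a secondary outcome.
- In-hospital deaths are complete, so the exposed part is deaths after discharge that take more than 99 days to be recorded.
- Both sections date the request, not the extraction. The article says obtaining data from organisations is a significant challenge, so real extracts may come later and 99 days is closer to a minimum.
- The direction is not uniform. An end-of-series deficit lowers the trend change but raises the step change. The 12-month effect used above is a summary chosen for this check. The article specifies a joint test of step and trend and places the margin on the post-versus-pre relative change.
- Applying the deficit to the last 13 weeks would give shifts of about -0.6%, -1.5% and -3%, but admissions up to 30 April already meet the six-month rule, so the wider window is not supported.

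The reply does not remove the contradiction. Any delay between request and extraction applies under either rule. If implementation slipped so that 31 October really was 15 months later, the six-month rule would move with it and the gap would be three months. The plan itself judged six months necessary and gave the reason.

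**Conclusion.** The point holds as an inconsistency with a one-sided risk to ascertainment. It is certain that the two sections disagree by 54 days on the printed dates, that 31 October 2020 is 16.3 and not 15 months after the last implementation, and that about 8 weeks of admissions, all post-implementation, would miss the plan's own six-month standard.

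A reader might infer that the 31 October date will leave deaths unrecorded, or that it will produce a false finding of non-inferiority. The documents do not support either. They give no reporting lag, the date lies beyond day 90 for every admission, and 30-day deaths are lost only if out-of-hospital reporting takes more than 99 days (39 days for 90-day deaths).

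Under the assumed shares of 2% to 10% missed in those 8 weeks, the 12-month effect moves by -0.4% to -2.0%. The upper end is 2.0/5 = 40% of the margin, but it needs a large fraction of out-of-hospital deaths to be missing. This is more than clerical, because the date sent to organisations decides how complete the mortality data are, but no serious bias has been shown.

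**What to change.** State one rule, in the same terms, in Follow-up and Statistical analysis.

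- **Preferred.** Request the final extract no earlier than six months after the last included admission, that is on or after 24 December 2020 on the planned dates, and change 15 months to 18 months. Cost: about 54 days' delay.
- **If 31 October 2020 must stay.** Correct the interval to about 16 months, amend the six-month statement, and restrict the mortality analyses, or a pre-specified sensitivity analysis, to admissions up to 30 April 2020. Cost: about 8 weeks of admissions out of roughly 4.4 years, for mortality only. The last organisation would keep 366 - 55 = 311 days of post-implementation mortality data, so the text should acknowledge the departure from 12 months' follow-up for that outcome.

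The rule should be settled before organisations are given a final request date.

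A reader might want the same six-month cut-off on every Data Monitoring Committee extract. That should not be adopted. The first review is about six months after phase III starts (Oversight), so the cut-off would remove nearly all main-trial post-implementation data from it, and interim procedures are left to the committee's Charter.
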